## 2.13 Follow-up

Patients will be assessed using self-administered questionnaires that will be filled in physically at the clinic at baseline, at the 5-week and 10-week treatment sessions, and then at the 26- weeks and 52-weeks (for only primary outcomes: disability) post-enrolment.

## 2.14 Compliance with treatment

A research assistant who is a staff member in department of physiotherapy, JSSCPT and not involved in low back pain treatment will assist participants to complete their questionnaires, which include self-reported measures of compliance with treatment. Day-to-day compliance with exercises will be monitored by the treating physiotherapists as part of their usual practice.

## 2.15 Data analysis

Data will be analyzed using IBM SPSS-V23.0 (SPSS Inc., Chicago, Illinois, USA) and Microsoft Excel^®^ (2010; Microsoft Corporation, Redmond, WA, USA).

***Analysis of patients’ clinical outcomes***

A descriptive summary of the characteristics of the patients will be provided at baseline. Continuous outcomes for patients will be analysed using linear mixed models (group × time interaction, with time modelled as a repeated measure) adjusting for baseline score. Ordinal outcomes will be analysed using the Mann-Whitney U test, while the risk ratio and number needed to treat will be evaluated using χ2 analyses. Analyses will focus on detecting between-group effects (with 95% CIs) at each time point (5, 10, and 26 weeks), and participants will be dichotomized according to whether they achieve the minimal clinically important difference (MCID) on outcome measures or not. The MCID for participants will be defined as 10/100 points for the Oswestry, 2/10 for the BPI pain scales, at least ‘much improved’ on the global rating of change scale, and ‘very satisfied’ on the treatment satisfaction scales. Given that these values may be too low in some contexts, the analyses will be repeated using a threshold of 50% reduction in Oswestry and NRS pain scores [14,56]. All data will be analysed according to intention-to-treat analysis (ITT), with missing data handled via maximum likelihood estimation ^[114]^.

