# Enrollment

Excluded (n = …) Not meeting inclusion criteria

(n = …)

Refused to participate (n = …)

Other reasons (n = …)

Randomized (n = 150)

Allocated to Usual care intervention

(n = 75)

Received allocated intervention (n = …)

Did not receive allocated intervention (n = …)

(give reasons)

Allocated to Individualised intervention

(n = 75)Received allocated intervention (n = …)

Did not receive allocated intervention (n = …)

(give reasons)

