## 2.3 Setting

The study will be conducted at Physiotherapy Outpatient Department (OPD) of JSS Hospital, Mysuru, India and the associated community centers affiliated to JSS Hospital.

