## 2.5 Sample size estimation

Sample size was calculated using G power using input parameters such as an effect size of 0.5, and power of 0.95. A sample size of 154 was received as an output from G power, allowing for loss to followup.

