6. *Psychosocial risk factors:* The Short-Form Örebro Musculoskeletal Pain Screening Questionnaire (ÖMPSQ-SF) will be used as a measure of psychosocial risk factors for chronic musculoskeletal pain ^[83,84]^. Although it is more commonly used as a prognostic screening tool at one point in time ^[85]^, in our trial the Orebro will also be administered at each follow-up point to detect changes in psychosocial risk factors over time. This appears justified given that Orebro has good test-retest reliability and internal consistency ^[83,86]^.
7. *Health-related quality of life:* Health-related quality of life will be measured with the EuoQol-5D-5L ^[87]^. Utilities will be calculated according to the validated algorithms of Dolan ^[88]^. The EuroQol-5D-5L has good reliability, validity, and ^responsiveness [89-91]^, and has been used in other low back pain trials ^[64,92]^.
8. *Mental health symptoms:* Mental health symptoms will be assessed using the 21-item Depression Anxiety and Stress Scale (DASS-21). The questionnaire measures the severity of depression, anxiety, and stress from normal to extremely severe ^[93]^. DASS-21 normal score cut-offs are 9 for depression, 7 for anxiety, and 14 for stress and higher scores suggest mild to extremely severe mental health symptoms ^[93]^. DASS-21 shows strong validity, test-retest reliability, internal consistency, and responsiveness ^[93,94]^.
9. *Confidence with activities:* Confidence with activities of daily living despite having pain will be assessed using the Pain Self-Efficacy Questionnaire (PSEQ). The PSEQ is a 10-item scale with a score ranging from 0 to 60, where high scores indicate greater levels of confidence in dealing with pain ^[95]^. The PSEQ has excellent validity, reliability, and responsiveness ^[96]^.
10. *Pain catastrophising:* The 13-item Pain Catastrophizing Scale (PCS) will be used to assess inappropriate coping strategies and catastrophic thinking about LBP. The scale is rated on a 5-point Likert scale ranging from 0 (not at all) to 4 (all the time) ^[97]^. Total scores range from 0 to 52, with higher scores indicating worse catastrophic thinking about LBP ^[97]^. The PCS has been shown to have adequate validity, reliability and responsiveness ^[97,98]^.

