
## APPENDIX: PATIENT REPORTED OUTCOMES

| **INITIAL PATIENT QUESTIONNAIRE** | | | | | | | | | | | |
| --- | --- | --- | --- | --- | --- | --- | --- | --- | --- | --- | --- |
| **Your details Patient Trial ID number _______________** | | | | | | | | | | | |
| **Title** | Mr | Mrs | | Family name (surname) | | | | | **Given name(s)** | | |
|  | Ms | Miss | |  |  |  |  |  |  |  |  |
| **Gender** | |  | | Date of birth *(dd/mm/yyyy)*__ __ /__ __ / __ __ __ __ | | | | | Today’s date *(dd/mm/yyyy)*__ __ /__ __ / __ __ __ __ | | |
|  | Male | Female | |  |  |  |  |  |  |  |  |
| Level of education | Primary | Secondary | | Tertiary (university) | | | | | None | | |
| What is your occupation? …………………………………………………………………………………………………… | | | | | | | | | | | |
| Annual household income?………………………………………………………………………………………………. | | | | | | | | | | | |
| Home address ………………………….………………………………………………………………………………………………………………………………. ………………………………………………………………………………………………………………………………………………………………….……………….  **Phone:** Home: ……………………………… Work: ……………………………….……….… Mobile: …………………………………..………………  **Email** ……………………………………………………………………………………………………………………………………………………………………….. | | | | | | | | | | | |
| **Country of Birth…………………………………………………………………………………………………………………….** | | | | | | | | | | | |
| **Do you require an interpreter?** | | | | | Yes | No | | | | | |
| *If you answered yes, please specify the language*………………………………………………………………… | | | | | | | | | | | |
| **Are you hearing or sight impaired?** | | | | | Yes | No | | | | | |
| **Do you require help with written or spoken communication?** | | | | | | | Yes | | | No | |
| **Tobacco use status (including smoking):**  Current user | | | | | | | Previous user | | | No | |
| **Height** *(in cm)* | | | **Weight** *(in kg)* | | | | | | | | |
| **Is there a compensation case relating to this episode?** | | | | | | | Yes | | | No | |
| **Marital status** | | | | Married | | | Unmarried | | | | |
|  |  |  |  | Divorced | | | Widow / widower | | | | |
| **How did your main pain begin?** | | | | | | | | | | | |
| Injury at home | | | | Car crash | | |  | | | | |
| Injury at work/school | | | | No obvious cause | | | |  | | | |
| Injury in another setting | | | |  | | |  | | | | |
| **How long has your main pain been present?** *(Tick* ***one*** *box only)* | | | | | | | | | | | |
| Less than 3 months | | | | 12 months to 2 years | | | More than 5 years | | | | |
| 3 to 12 months | | | | 2 to 5 years | | |  | | | | |

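### The outcome model leaves baseline ÖMPSQ-SF unused: valid as written, but one pre-specified covariate could add a little precision at almost no cost

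*Protocol*

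**What the plan says.** Protocol section 2.15 (Analysis of patients' clinical outcomes) fits linear mixed models with a group-by-time interaction, "with time modelled as a repeated measure) adjusting for baseline score". No other covariate is named. Ordinal and dichotomised outcomes are handled by other tests and are not affected by this point.

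The protocol holds more baseline information than that model uses:

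- **Örebro short form.** Table 2 schedules it at weeks 0, 5, 10 and 26, and section 2.8 applies the baseline assessments to both groups. Section 2.12, item 6, introduces it with the words "Although it is more commonly used as a prognostic screening tool at one point in time" before justifying repeated use. Appendix 2 treats a high Örebro total as a sign that psychosocial or neurophysiological factors may hinder recovery. Its cut-off of 105 is above the 100 that the printed form can give (ten items, each scored to at most 10). I therefore take that passage only as a statement of what the investigators believe, not as a rule for this form.
- **Pain duration.** The initial patient questionnaire asks "How long has your main pain been present" in categories.
- **Place of treatment.** Section 2.3 names the hospital outpatient department and "the associated community centers affiliated to JSS Hospital". Section 2.9 specifies block randomisation and names no stratification factor.

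**The concern.** In a randomised trial, adjusting for a baseline variable that predicts the outcome narrows the confidence interval for the treatment effect. The outcome's own baseline value is usually the strongest such variable, and the model already has it. A prognostic score measured before treatment in every patient is the natural next candidate, and here it needs no new data collection.

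The stake is precision only. The trial has limited precision to spare: the flow chart plans for 150 patients, and the stated power is not reached at that number under a simple two-sample test (see the working). Pre-specification matters because a covariate added after the data have been seen invites the charge that it was chosen for its result.

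**Working it through.** **The plan's own figure.** Section 2.5 gives an "effect size of 0.5, and power of 0.95" and then: "A sample size of 154 was received as an output from G power, allowing for loss to followup". Neither the significance level nor the dropout rate is stated. I assume a two-sided 5% level because section 2.15 reports 95% intervals: "Analyses will focus on detecting between-group effects (with 95% CIs) at each time point (5, 10, and 26 weeks". A two-sample t-test with these inputs needs 105 per arm, 210 in total, before any loss (176 in total if one-sided). The 154 is not reproduced. The flow chart has "Randomized (n = 150", 75 per arm, which gives power of 0.86 by the t-test before loss. That discrepancy is a separate and larger matter that a covariate does not cure. I use 150 below because it is the number to be randomised.

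**Effect of one added covariate.** Two things act on the variance of the treatment estimate at a given time point:

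- residual variance is multiplied by (1 − R²), where R² is the partial R² of ÖMPSQ-SF beyond the outcome's baseline score;
- estimating k extra coefficients inflates the variance by (N − 4)/(N − 4 − k).

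So v = (1 − R²) × (N − 4)/(N − 4 − k). Confidence-interval width changes by √v − 1, and the equivalent sample size is N/v. With N = 150 and k = 1 the inflation is 146/145 = 1.0069.

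| Assumed partial R² | v | Change in CI width | Equivalent N |
|---|---|---|---|
| 0 | 1.0069 | 0.3% wider | 149 |
| 0.05 | 0.9566 | 2.2% narrower | 157 |
| 0.10 | 0.9062 | 4.8% narrower | 166 |

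Break-even is at 1 − R² = 145/146, so R² = 1/146 ≈ 0.007.

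**If one hospital/community indicator is also added (k = 2).** The inflation is 146/144 = 1.0139. The interval becomes 0.7% wider, 1.9% narrower or 4.5% narrower at the same three values, where R² is now the joint partial R² of both terms. Break-even is 2/146 ≈ 0.014.

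**After loss to follow-up.** With an assumed 20% loss (N = 120, k = 1), the worst case is √(116/115) − 1 = 0.4% wider, and break-even is 1/116 ≈ 0.009. The conclusion does not change.

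**In terms of power.** By the normal approximation at a standardised effect of 0.5 and 75 per arm, power = Φ(0.5 × √(75/2) / √((1 − r²) × v) − 1.96). Here r is the correlation between the outcome and its own baseline, which the protocol does not give.

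| Assumed r | Model as planned | R² = 0 | R² = 0.05 | R² = 0.10 |
|---|---|---|---|---|
| 0 | 0.865 | 0.862 | 0.879 | 0.896 |
| 0.5 | 0.942 | 0.941 | 0.951 | 0.960 |

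The r = 0.5 row is the fairer kind of comparison, because the planned model already adjusts for baseline. There the gain is about 1 to 2 percentage points.

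**The case against.** The strongest reply is that nothing here is wrong. Baseline-score adjustment is valid and unbiased, no stratification factor is left out because none is named, and a fuller covariate list is often left to a statistical analysis plan, which is not shown. All of that stands. The point is confined to improving a model that section 2.15 does specify.

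The reply also says the gain may be nil, and this stands too. The protocol gives no R² or correlation. Several Örebro items sit close to the outcomes: past-week pain resembles the pain rating scale, and the light-work and sleep items resemble Oswestry sections 10 and 7. Much of what the score predicts may already be carried by the baseline outcome. What the reply does not overturn is the asymmetry: a useless term widens the interval by about 0.3%.

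A reader might infer more than the documents support:

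- **That pain duration should also be added.** Eligibility limits duration to more than 3 months, and item 1 of the Örebro form already scores it, so a separate term is partly redundant.
- **That site is being ignored although it is on file.** The baseline questionnaire has no site field, and neither the number of community centres nor their share of patients is given. Nothing says site predicts outcome beyond baseline.
- **That chance imbalance biases the estimate.** It does not. Randomisation makes such imbalance part of the sampling variation that the interval already covers.
- **That the precision is free.** Each term costs a degree of freedom. With two terms plus five separate centres (six added terms), break-even rises to a partial R² of 6/146 ≈ 0.04.

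**Conclusion.** The planned model is sound. It omits one baseline score that the protocol collects in both arms and itself describes as prognostic, and adding that score is a small, inexpensive improvement. If ÖMPSQ-SF explains 5 to 10% of the variance left after the baseline score, the interval narrows by 2.2 to 4.8%. If it explains nothing, the interval is about 0.3% wider. Those R² values are assumptions, and the protocol cannot say which applies. The calculation also assumes 150 analysed patients and a single comparison at one time point. The point is optional. It does not bear on the validity of the trial, and it is no remedy for the sample-size calculation.

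**What to change.** In section 2.15, before unblinding, add one sentence: the linear mixed models for continuous outcomes other than ÖMPSQ-SF include the baseline ÖMPSQ-SF total (the ten-item form in the appendix) as a fixed effect, alongside the baseline score of the outcome. The exception is needed because ÖMPSQ-SF is itself a continuous outcome, and its baseline would otherwise enter its own model twice.

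If place of treatment is recorded for every patient, a single hospital/community indicator may be pre-specified as well. Separate terms for each centre, and a separate duration term, are best left out.

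The cost is one line of specification and one degree of freedom (two with the site indicator). No new data are needed for ÖMPSQ-SF. The site indicator needs confirmation that site is captured. The risk is that nothing is gained if ÖMPSQ-SF adds no information beyond the baseline score.

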## 2.8 Baseline evaluation

In addition to demographic and general health information of the participant, all the outcome measures (Table 2) provided below will be evaluated at baseline for both STOPS group as well as standard physiotherapy group. All the baseline assessment will be performed by a Physiotherapist who has a minimum of bachelor level degree and blinded allocation of the groups.

| **Patients’ outcome measures** | |
| --- | --- |
| **Outcome measures** | **Measurement points (**weeks) |
| **Primary outcome measures** | |
| 1. Oswestry Disability Index V2.1 with “sex life” question replaced by a “work/housework” question | 0, 5, 10, 26 and 52 |
| 2.Back pain and leg pain intensity :NPRS | 0, 5, 10, 26 and 52 |
|  |  |
| 3. Resting state functional MRI | 0,26 |
| **Secondary outcome measures** | |
| 1. Brief Pain Inventory | 0, 5, 10, 26 |
| 1. Global rating of change scale (7-point Likert scale) | 5, 10, 26 |
| 1. Satisfaction with treatment (5-point Likert scale) | 5, 10, 26 |
| 1. Interference with work or housework in the past week (5-point Likert scale) and number of hours missed at work in past week. | 0, 5, 10, 26 |
| 1. Örebro Musculoskeletal Pain Screening Questionnaire (ÖMPSQ-SF) | 0, 5, 10, 26 |
| 1. Quality of life (EuroQol-5D-5L) | 0, 5, 10, 26 |
| 1. Depression Anxiety and Stress Scale (DASS-21) | 0, 5, 10, 26 |
| 1. Pain Self-Efficacy questionnaire (PSEQ) | 0, 5, 10, 26 |
| 1. Pain Catastrophizing Scale (PCS) | 0, 5, 10, 26 |
| 1. Insomnia Severity Index (ISI) | 0, 5, 10, 26 |
| 1. Central Sensitisation Inventory (CSI) | 0, 5, 10, 26 |
| 1. Clinical inflammation score | 0, 5, 10, 26 |
| 1. Treatment Credibility Questionnaire | 5, 10, 26 |
| 1. Healthcare utilisation | 5, 10, 26 |
| 1. Compliance with treatment | 5, 10, 26, 52 |
| 1. Resting state functional MRI | 0, 26 |
| 1. Qualitative interviews | At the end of treatment trial 10 |
| 1. Adverse event | 5, 10, 26 |

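### The five-point work-interference outcome is tested with an unadjusted Mann-Whitney test, which leaves its scheduled baseline unused and supplies no estimate for the promised 95% CI

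*Protocol*

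**What the plan says.** Section 2.15 of the protocol, under the analysis of patients' clinical outcomes, assigns a method to each type of outcome.

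- Continuous: linear mixed models ("group × time interaction, with time modelled as a repeated measure) adjusting for baseline score").
- Ordinal: "Ordinal outcomes will be analysed using the Mann-Whitney U test".
- Responders: "the risk ratio and number needed to treat will be evaluated using χ2 analyses".

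It then says "Analyses will focus on detecting between-group effects (with 95% CIs) at each time point", listing weeks 5, 10 and 26, and does not limit this to continuous outcomes. Baseline adjustment is stated for the mixed models only.

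Table 2 (section 2.8) lists three clearly ordinal Likert outcomes. "Interference with work or housework in the past week (5-point Likert scale") is scheduled at weeks 0, 5, 10 and 26. Global rating of change (7 points) and satisfaction with treatment (5 points) are scheduled at weeks 5, 10 and 26 only.

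Responder rules are given for the Oswestry, the BPI pain scales, global change and satisfaction. None is given for work interference.

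**The concern.** Work interference is the one clearly ordinal outcome with a week-0 value of its own in Table 2. A two-sample rank test at each visit makes no use of that value, while the continuous outcomes beside it are adjusted. Precision is lost although the data needed to recover it are already scheduled.

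The second gap is in reporting. A Mann-Whitney test, as named, returns a p-value. The protocol names no companion estimator, such as a Hodges-Lehmann shift, a probability index or an odds ratio. Because the item is not dichotomised, it gets no risk ratio either. The interval promised at each time point therefore has no source for this outcome.

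**Working it through.** **No figure to reproduce.** The protocol states no power for any ordinal outcome. The effect size of 0.5 in section 2.5 is not tied to one.

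**Which ordinal outcomes are affected**

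| Outcome | Week 0 in Table 2 | Responder rule, hence risk ratio |
|---|---|---|
| Work interference | yes | no |
| Global rating of change | no | yes |
| Satisfaction with treatment | no | yes |

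Only the first row lacks both the use of its own baseline and an effect estimate.

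**Power lost by leaving baseline out**

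*Input from the protocol:* 75 per arm (flow chart, Figure 1).

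*Assumptions, not in the protocol:* a latent normal baseline x; a latent outcome y = r·x + √(1 − r²)·e − d·arm, with r = 0.3, 0.5 or 0.7 and d = 0.4 or 0.5 SD; two-sided 5% tests. Both variables are cut into five categories. In runs B and C the control proportions are 10, 25, 30, 25 and 10%.

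- Run A: 300 trials per row, adjusted proportional-odds model, d = 0.4.
- Run B: 2,000 trials per row, baseline-adjusted analysis of ranks, d = 0.5.
- Run C: 2,000 trials per row, proportional-odds model with arm and baseline category (Wald test), both shifts.

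| Run | d | r | Mann-Whitney | Adjusted | Gain (points) |
|---|---|---|---|---|---|
| A | 0.4 | 0.3 | 65.7% | 71.3% | 5.6 |
| A | 0.4 | 0.5 | 65.3% | 75.3% | 10.0 |
| A | 0.4 | 0.7 | 62.3% | 85.7% | 23.4 |
| B | 0.5 | 0.3 | 84.1% | 86.1% | 2.0 |
| B | 0.5 | 0.5 | 81.4% | 89.2% | 7.8 |
| B | 0.5 | 0.7 | 81.9% | 96.4% | 14.5 |
| C | 0.4 | 0.3 | 62.2% | 65.5% | 3.3 |
| C | 0.4 | 0.5 | 63.2% | 73.2% | 10.0 |
| C | 0.4 | 0.7 | 63.6% | 86.2% | 22.6 |
| C | 0.5 | 0.3 | 82.0% | 85.7% | 3.7 |
| C | 0.5 | 0.5 | 81.8% | 89.6% | 7.8 |
| C | 0.5 | 0.7 | 82.7% | 97.0% | 14.3 |

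The simulation error of one power figure is √(p(1 − p)/runs). For run A this is √(0.65 × 0.35/300) = 2.8 points. With 2,000 runs it is √(0.73 × 0.27/2000) = 1.0 point. Run A's 5.6 at r = 0.3 is therefore a loose upper figure. The 10.0 at r = 0.5 is quoted with one point of tolerance, as 8 to 11.

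With no treatment effect (d = 0), rejection rates were 4.5 to 5.4% for Mann-Whitney in runs B and C, 4.1 to 5.7% for the adjusted rank analysis and 5.7 to 6.2% for the proportional-odds Wald test. Mann-Whitney is valid. About one point of run C's gain may reflect the slightly liberal Wald test.

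**Responder outcomes**

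*Assumptions:* Oswestry mean 40 and SD 15, control improvement of 10 points, extra effect 0.5 × 15 = 7.5 points, 2,000 trials per row. Chi-square is compared with logistic regression on arm and baseline.

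| Rule | r | Chi-square | Adjusted | Gain (points) |
|---|---|---|---|---|
| 10 points | 0.3 | 56.6% | 63.5% | 6.9 |
| 10 points | 0.5 | 67.9% | 73.5% | 5.7 |
| 10 points | 0.7 | 87.1% | 89.2% | 2.1 |
| 50% reduction | 0.3 | 67.1% | 67.5% | 0.4 |
| 50% reduction | 0.5 | 75.1% | 74.9% | −0.2 |
| 50% reduction | 0.7 | 86.8% | 88.2% | 1.4 |

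Gains are taken before rounding. A further run with shifts of 0.4 to 0.5 SD gave −1 to +7 points for the 10-point rule. A fair summary is 0 to 7 points for that rule and 0 to 1 for the 50% rule.

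**The case against.** The strongest reply is that nothing here is an error. Mann-Whitney and chi-square are valid under randomisation, and chance imbalance at baseline does not bias them. The primary Oswestry analysis is already adjusted. Mann-Whitney also has standard companion estimates with intervals, and the SAP, which is not at hand, may name one. All of that stands, and it limits the point to efficiency and reporting. It does not remove it: the protocol itself fixes the test, names no estimator and promises an interval.

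Three stronger readings are tempting, and the protocol does not support them.

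- *All ordinal outcomes are deprived of baseline adjustment.* Global change is itself a rating of change since baseline, and treatment satisfaction has no week-0 value in Table 2. The baseline form asks about satisfaction with earlier care, which is a different question.
- *All ordinal outcomes lack an effect estimate.* Global change and satisfaction are also dichotomised, and a risk ratio and number needed to treat can carry intervals.
- *The responder analyses ignore baseline.* The rule "the analyses will be repeated using a threshold of 50% reduction in Oswestry and NRS pain scores" is computed from baseline, and the 10-point Oswestry and 2-point BPI rules read as change from baseline. What is missing is a covariate, and its gain is small.

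One caution bears on the fix. Table 2 schedules the five-point item at week 0, but I did not find it on the initial patient questionnaire in the appendix as I read it. That form has a 0–10 rating of productivity at work and the 0–10 BPI item on normal work. The item's presence at baseline should be confirmed.

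**Conclusion.** The point holds for one secondary outcome. As the protocol stands, work interference loses the adjustment given to continuous outcomes and has no estimate to carry the promised 95% CI.

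The loss is about 2 to 4 power points at a baseline correlation of 0.3 (up to 6 in the 300-trial run), about 8 to 11 at 0.5 and about 14 to 23 at 0.7. These sizes rest on an assumed shift of 0.4 to 0.5 SD, a five-level scale and assumed correlations, none of which the protocol gives for this item. The missing interval depends on none of these assumptions.

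The consequence is lost precision and an incomplete report. It is not bias or an invalid test. The change is worth making because it is cheap, but the trial's main conclusion does not depend on it.

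**What to change.** In section 2.15, analyse work interference at each time point with a proportional-odds model containing arm and baseline category, and report the common odds ratio with 95% CI. Keep Mann-Whitney as a sensitivity analysis, because the new model relies on the proportional-odds assumption. Leave global change and satisfaction as they are: own-baseline adjustment does not apply to them, and they already receive a risk ratio.

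Optionally, for the Oswestry and pain responders, add a modified Poisson model with arm and baseline score to give an adjusted risk ratio with 95% CI. Keep the unadjusted risk ratio and number needed to treat, since the adjusted model does not give the latter directly.

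The cost is a few lines of analysis text. The models are available in SPSS, and visits and sample size do not change. The only check needed on data collection is that the five-point item is actually on the week-0 form, as Table 2 requires.

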***Secondary outcomes***

1. *Back pain and leg pain intensity:* Separate 0-10 Numerical Rating Pain Scales will be administered, one for back pain and another for leg pain. The intensity of pain will be rated on average over the past week, with end-point descriptors of “no pain” and “worst pain possible”.
2. *Pain severity and impact:* Brief Pain Inventory - Short Form (BPI-SF) will be used to assess the severity of pain and the impact of pain on daily functions. The BPI-SF is a 9-item self-administered questionnaire which exists within the [biopsychosocial model](https://www.physio-pedia.com/Biopsychosocial_Model) of pain, as it addresses sensory, emotional, and functional aspects of the pain experience ^[72]^. Thus, the tool is responsive to changes in pain associated with both pharmacological, physical, and psychological interventions^[73]^
3. *Global effect:* Global rating of change will be measured using a 7-point Likert scale, with participants rating their overall change since the baseline assessment as “completely recovered”, “much improved”, “slightly improved”, “no change”, “slightly worsened”, “much worsened”, or “vastly worsened”.^[74-75]^ Various versions of this scale are reliable, responsive, and valid. ^[75-76]^
4. *Satisfaction with treatment:* Participants will rate their satisfaction with physiotherapy treatment on a 5-point Likert scale, with ratings from “very satisfied” to “very dissatisfied”.^[77,78]^This scale has good reliability, validity, and responsiveness. ^[79,80]^
5. *Work interference:* Interference with work due to the LBP will be assessed in two ways. Firstly, at each assessment point, participants will record the number of workdays missed due to their back/leg condition over the previous 30 days. ^[14,56]^ Secondly, participants will rate the degree of interference with work (employment or housework) caused by their back/leg condition over the previous week on a five-point scale ranging from “not at all” to “extremely”. ^[14,56]^ These measurement methods have demonstrated good reliability, validity, and responsiveness ^[81,82]^.

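### The 2-point pain MCID is set on the Brief Pain Inventory but its 50% repeat is set on the NRS, so for pain the second responder analysis does not repeat the first

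*Protocol*

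**What the plan says.** Section 2.15, under the analysis of patients' clinical outcomes, plans a responder analysis in which "participants will be dichotomized according to whether they achieve the minimal clinically important difference (MCID) on outcome measures or not". It fixes four thresholds. The Oswestry one is given first: "The MCID for participants will be defined as 10/100 points for the Oswestry". For pain it is "2/10 for the BPI pain scales". The other two are categories on the global rating of change and on treatment satisfaction.

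A second pass follows. Its reason is stated as "Given that these values may be too low in some contexts", and its content is that "the analyses will be repeated using a threshold of 50% reduction in Oswestry and NRS pain scores".

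Elsewhere the protocol treats the two pain instruments as different outcomes. Table 2 (section 2.8) has the row "2.Back pain and leg pain intensity :NPRS" under primary outcomes and puts the BPI on its own row under secondary outcomes. Section 2.12 describes the first as "Separate 0-10 Numerical Rating Pain Scales will be administered, one for back pain and another for leg pain". It describes the second as a separate item: "Brief Pain Inventory - Short Form (BPI-SF) will be used to assess the severity of pain and the impact of pain on daily functions". The questionnaire appendix prints the back and leg scales and the BPI as separate forms.

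**The concern.** The second pass is a sensitivity analysis. It asks whether the responder conclusion survives a different definition of response, given the protocol's own doubt about the first set of values. That question is answered cleanly only if the threshold alone changes. For the Oswestry it does. For pain, the threshold and the instrument change in the same step, so the 50% result is not a repeat of the 2-point result.

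It also leaves a gap in the results. The back and leg NRS would have no risk ratio or number needed to treat at an absolute MCID, although Table 2 lists it as a primary outcome. The BPI would have no 50% result.

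**Working it through.** No sample size, power or alpha figure is involved, so there is no planned number to reproduce. The check sets the stated rules side by side.

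**Step 1. Which threshold attaches to which instrument (section 2.15).**

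| Measure | Absolute MCID | 50% reduction |
| --- | --- | --- |
| Oswestry | 10/100 | yes |
| BPI pain scales | 2/10 | not stated |
| Back and leg NRS | not stated | yes |
| Global rating of change | category | not applicable |
| Treatment satisfaction | category | not applicable |

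Only the Oswestry has an entry in both columns. No absolute MCID for the back or leg NRS appears anywhere else in the protocol, and no 50% rule is given for the BPI.

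**Step 2. Whether the two pain instruments could be the same thing.** Table 2 and section 2.12 list them separately. The NRS is two ratings, one for the back and one for the leg. The BPI form in the appendix asks for worst, least, average and current pain, and none of these ratings is split into back and leg. A BPI responder result therefore cannot stand in for a back pain or a leg pain responder result.

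**Step 3. Why the two thresholds need a common scale.** On one 0-10 scale with baseline score b, the MCID rule asks for a fall of at least 2 points and the 50% rule asks for a fall of at least b/2. The second is the stricter only when b/2 > 2, that is, when b > 4.

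| Baseline b | Fall needed under the 50% rule (b/2) | Fall needed under the MCID rule |
| --- | --- | --- |
| 2 | 1.0 | 2 |
| 3 | 1.5 | 2 |
| 4 | 2.0 | 2 |
| 5 | 2.5 | 2 |
| 6 | 3.0 | 2 |

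Table 1 excludes only pain scores below 2/10, so baselines of 2 to 4 can occur. How the two rules compare depends on the patient's baseline on the scale in use. With one rule read on the BPI and the other on the NRS, two baselines are in play and that comparison is lost.

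**The case against.** Four points can be made on the other side.

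- **It may be a slip of terminology.** The BPI pain items are also 0-10 numerical ratings, so NRS could be loose shorthand for them, or BPI could be a slip for NRS. Either is possible. But the protocol uses the numerical rating scale name for the separate back and leg scales and calls the other instrument the BPI. If the BPI was meant throughout, back and leg pain would have no responder analysis at all. The sentence needs correcting on any reading.

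- **The consequence is narrow.** This stands. Pain is also analysed as a continuous outcome by linear mixed model with between-group effects and 95% confidence intervals. The back and leg NRS is fully covered there and keeps its 50% responder analysis. The Oswestry has both thresholds.

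- **The mismatch need not distort a group comparison.** A reader might infer that changing instrument would materially bias the responder result. The documents give no figures to support that. In an illustrative simulation, all of whose inputs are assumptions (baseline mean 5.5, SD 1.7; mean fall 2.4 against 1.8, SD 2.0; reporting error SD 0.5, 0.8 or 1.0 on each scale; baseline NRS of at least 2), the 2-point risk ratio was 1.195, 1.183 and 1.172 on the NRS and 1.192, 1.181 and 1.167 on the BPI average item. The 50% risk ratio on the NRS was 1.276, 1.266 and 1.249. Changing instrument moved the ratio by 0.005 or less, and changing threshold moved it by about 0.08. The model assumes that both scales measure the same underlying pain, so it says nothing about leg pain, where they could diverge. It does rule out presenting the mismatch as a demonstrated bias.

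- **The plural in the BPI threshold proves little.** A reader might infer that four BPI ratings leave the responder result open to selection. The text does not say that four responder analyses are planned, and choice of item and scoring are commonly left to the statistical analysis plan, which is not shown.

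**Conclusion.** The point holds as an internal inconsistency in section 2.15. The text promises a repeat and, for pain, specifies a different analysis on a different instrument. The back and leg NRS lacks an MCID responder analysis, the BPI lacks a 50% one, and only the Oswestry is repeated as described.

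The size is modest. It affects the supplementary risk ratios and numbers needed to treat for pain, not the continuous analysis. No bias in a reported result has been shown.

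The conclusion rests on one reading: that NRS in section 2.15 means the back and leg scales so named in Table 2 and section 2.12. It does not depend on whether those scales are primary (Table 2) or secondary (section 2.12), since the mismatch is the same either way. It is still worth correcting, because the rule as stated does not do what it says and the correction is nearly free.

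**What to change.** In section 2.15, name the same pain scales at both thresholds. The most direct wording applies the 2/10 MCID and the 50% reduction to the back pain NRS and, separately, to the leg pain NRS. If a BPI responder analysis is kept, apply both thresholds to it as well. Any choice that keeps one instrument across both thresholds restores the repeat. Using the NRS has the advantage of covering the pain outcome that Table 2 lists as primary.

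The cost is one sentence and a few extra responder tables. Both instruments are already collected at weeks 0, 5, 10 and 26, which covers the time points at which section 2.15 makes its comparisons. The change should be made before unblinded outcome data are seen.
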